#### Secondary outcome measures

We will employ secondary outcomes that we expect to change as a result of the intervention and could explain the effect of the intervention on the primary outcomes; including the measurement of autonomy support, perceived competence, autonomous and controlled motivation, as well as fear avoidance as it relates to physical activity.

#### Moderating variables

We will also measure specific individual factors at baseline that could influence the treatment effect. These include the therapist’s personality (causality orientations) and motivation to participate in the study, the therapist and patient’s treatment expectations, and the patient’s baseline levels of depressive symptoms. Descriptions and references for these measures are presented in Appendix A.

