#### Patients

##### Baseline assessment

A schematic view of the assessment time line for patients is presented in Table 3. The baseline assessment is a self-report questionnaire regarding the patient’s demographic data, LBP history, primary and secondary outcome data, as well as assessments of potential moderating variables. The assessment will take approximately 20 minutes to complete and will be completed at the physiotherapy site administered by the Research Physiotherapist or in cases in which this does not suit the patient’s schedule, he/she can complete the assessment by telephone (maximum 48 hours before his/her physiotherapy appointment). Directly after the initial physiotherapy appointment, the patient will be given a pedometer and asked to complete two short questionnaires about his/her perceptions of the physiotherapist’s autonomy support and the patient’s motivation to follow the physiotherapist’s advice.

**Table 3 T3:** Outcome assessment timeline

**Variable**	**Pre-randomization**	**Baseline Pre-treatment**	**Baseline Post-treatment**	**Week1**	**Week4**	**Week12**	**Week24**
**Demographics**		✓					

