**Moderating Variables**							
Expectation of treatment	*		✓				
Patient depression		✓					
Physiotherapist’s general causality orientations	*						
Physiotherapist’s autonomous and controlled motivation for participation in training.	*						

Note: ✓ = patient rated assessment. * = physiotherapist rated assessment. # = physiotherapist rating of patient behavior following each treatment session (most likely to occur during first 12 weeks following initial session).

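### Patient treatment expectation is listed as a baseline moderator, but Table 3 schedules the patient's only rating after the first physiotherapy session, when the randomized intervention may already have influenced it

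*Protocol article*

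**What the plan says.** The Moderating variables paragraph under Outcomes opens with "We will also measure specific individual factors at baseline that could influence the treatment effect". Its list includes "the therapist and patient’s treatment expectations, and the patient’s baseline levels of depressive symptoms".

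The Baseline assessment paragraph for patients describes a self-report questionnaire completed at the physiotherapy site or by telephone ahead of the first appointment. Its contents include "primary and secondary outcome data, as well as assessments of potential moderating variables". The same paragraph then describes two short questionnaires given straight after the first appointment, on the physiotherapist's autonomy support and on motivation.

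Table 3 divides baseline into a pre-treatment column and a column headed "Baseline Post-treatment". The row "Expectation of treatment" carries an asterisk under Pre-randomization, nothing under Baseline Pre-treatment, and a tick in the post-treatment column. The table's note defines the tick and then the asterisk: "patient rated assessment. * = physiotherapist rated assessment". The asterisk is therefore the therapist's rating, and the tick is the patient's only rating. The row "Patient depression", the other patient-rated moderator, has its tick under Baseline Pre-treatment.

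**The concern.** A moderator should describe the patient before the randomized exposure begins. In this trial the exposure is how the physiotherapist communicates, and the patient first meets it in the first session. If expectation is rated only after that session, the two arms may differ on it because of the intervention. An interaction between arm and that rating would then mix two questions: whether patients who came in with higher expectations respond differently, and whether the intervention works partly by raising expectations.

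The timing is fixed at data collection. Without a pre-session rating, no later analysis plan can recover one. What is at stake is the interpretability of this one moderator, not the trial's main comparisons.

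**Working it through.** No sample size, power or error-rate figure bears on this point, so there is nothing to recalculate. The check sets the places side by side.

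1. **Role.** Outcomes (Moderating variables), Table 3 and Appendix A all class expectation as a moderator. It is not listed among the primary or secondary outcomes, and it is not among the mediators in hypothesis 5.

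2. **Timing in the text.** The baseline questionnaire includes "as well as assessments of potential moderating variables". The telephone version must be done no more than 48 hours ahead of the appointment, and the section on potential inconveniences places the 20-minute assessment before the first appointment. On this reading the patient's expectation is rated before treatment.

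3. **Timing in Table 3.** The seven time columns are Pre-randomization, Baseline Pre-treatment, Baseline Post-treatment, and Weeks 1, 4, 12 and 24.

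| Row | Pre-randomization | Baseline Pre-treatment | Baseline Post-treatment |
|---|---|---|---|
| Expectation of treatment | therapist | empty | patient |
| Patient depression | empty | patient | empty |
| Perceived competence | empty | patient | patient |
| Autonomous and controlled motivation | empty | patient | patient |

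The neighbouring rows line up with the header, so the expectation row does not look displaced by the conversion from PDF.

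4. **Whether the first session counts as exposure.** The Treatment fidelity section rates strategy use only on initial appointments, so the protocol itself treats the intervention as active then. Table 2 lists giving a rationale and offering choice among the strategies taught. Both could plausibly change what a patient expects from treatment.

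5. **Consequence.** Let E0 be expectation before the first session and E1 expectation after it. If the session shifts expectation by an amount that depends on arm, then E1 = E0 + shift(arm). Patients with the same E1 in the two arms would then differ on average in E0, so an arm-by-E1 interaction does not compare like with like. Table 3 never collects the patient's E0, so the shift can be neither estimated nor removed.

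6. **Contrast within the protocol.** Perceived competence and motivation are rated both before and after the first session and are classed as outcomes expected to respond to the intervention. Expectation is rated at the same post-session point, has no earlier value, and is classed as a moderator.

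7. **Reach.** Statistical methods describes mixed models with arm as predictor, fidelity comparisons, and a structural equation model of Figure 2. It names no interaction with expectation and no adjustment for it.

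**The case against.** The strongest reply is that no stated analysis uses the variable. That is correct, and it confines the point to moderator or covariate use. A reader might infer that the estimated treatment effect would be diluted by adjusting for expectation, and might try to put a figure on the loss. The documents do not support this. No such adjustment is planned, and the two inputs needed (the shift in expectation and its correlation with outcome) are not given.

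A reader might also infer that the rating has already been changed by the intervention. The documents contain no data on any such shift. They support only that the rating is open to being affected.

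A third reply is that both columns carry the word baseline, so the Outcomes paragraph does not literally contradict Table 3. That stands for the Outcomes paragraph alone. It does not settle the conflict with the Baseline assessment text, which puts moderators in the questionnaire completed before the appointment, and the label does not alter the order of events.

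It is tempting to add that expectation is missing from the two post-session questionnaires named in the text. This is weak evidence: Table 3 also schedules perceived competence after the session, and the text does not name that either.

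Finally, the tick may simply be in the wrong cell. That is possible. The table is nevertheless the stated assessment timeline, and staff who follow it would collect the rating too late.

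**Conclusion.** The point holds in a limited form. Text and table disagree on when the patient rates expectation. If Table 3 is followed, the rating comes after first exposure to the randomized communication style and cannot serve as a pre-exposure moderator. It affects one of the two patient-rated moderators, for every patient enrolled (292 planned). It does not touch the therapist's pre-randomization rating or the primary and secondary comparisons. No numerical bias is claimed.

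The conclusion rests on two assumptions: that the Table 3 row is printed as intended, and that experimental-arm physiotherapists have been trained before they see study patients, as the fidelity assessment of initial appointments implies.

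**What to change.** Reconcile Table 3 with the Baseline assessment and Moderating variables text by moving the patient's tick for expectation to the Baseline Pre-treatment column and placing the rating in the existing pre-session booklet. Appendix A describes it as a numerical rating scale, so the cost is one short rating moved from one booklet to another, with no added visit.

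If a post-session rating is wanted as well, or is all that has been collected, label it a process variable in Table 3 and Appendix A, and state that it will not be used as a moderator or baseline covariate. That costs only a change of wording. The therapist's rating needs no change.

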### Treatment fidelity

Audio-recordings will be used to assess fidelity of treatment. For this outcome, at least 20% of the physiotherapists in the control arm and at least 20% of physiotherapists in the experimental arm will be asked to audio record one of their treatment sessions with a study participant. These sessions must be an initial (week 1) appointment. Each audio recording will be assessed by an expert rater, who will be blinded to specific study hypotheses and allocation of the physiotherapist to the experimental or control arm. Raters will assess the overall autonomy support provided. Using a tool that will be designed specifically for this study, they will also rate the quality of the physiotherapist’s use of the 18 strategies taught during the communications skills workshops (i.e., fidelity).

### Data integrity

The research team will monitor the integrity of trial data. For physiotherapist treatment record form data, which are slightly different between experimental and control arms (i.e., 5A prompts described in the intervention section), a research investigator un-blinded to treatment allocation will perform regular data checks during data entry and provide feedback to physiotherapists regarding data omissions where necessary. For patient data, a blinded investigator will enter data within 72 hours of patient completion and follow-up with patients regarding missing data that could be salvaged. All data will be double entered, to detect and correct input errors.

### Sample size

The sample for the study was calculated using data from our recent pilot study [36]. The effect sizes observed in that investigation were *d* = .4 for adherence and satisfaction with back pain, and *d* = .5 for PA-walking behavior. These effect sizes are similar to those reported in a recent Cochrane review of trials investigating the effectiveness of interventions designed to increase adherence among chronic pain patients [16]. As a result, the estimated sample required for 80% power (α = .05) to detect a between arm effect of d = .4 in a non-clustered RCT, using a t-test, would be 156 (*n* = 78 per arm).

To account for the clustered nature of the data, we multiplied this sample size by a correction factor of 1 + (*m* − 1)ρ, where *m* was the mean expected cluster size and ρ was the anticipated intracluster correlation coefficient [38]. Based on previous research in clinical settings regarding physical activity in patients with CLBP [18,23], we estimated that the ICC would be 0.03. Assuming we recruit *m* of 22 patients per clinic, the correction factor is 1.63 for our cluster-randomized design. To account for the clustered design, the study would require 254 participants to achieve 80% power for the adherence and LBP related data.

We anticipate that approximately 15% of participants will not complete follow-up assessments [39]. Traditionally, one would account for this loss to follow up and increase the sample size by 15% to 292 participants (146 per arm). However, as our method of analysis (linear mixed models, see statistical methods section) does not require list-wise deletion, and therefore loss to follow-up is expected to have negligible impact. Indeed, Chakraborty and Gu [40] demonstrated that up to 20% of the observations can be missing without a meaningful loss of power for mixed modeling approaches. As such, our intended sample of 292 patients will provide more than 80% power to detect significant effects in these primary outcomes.

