### Hypotheses

1. Patients in the experimental arm will report significantly greater weekly physical activity (PA) participation compared with their pre-treatment PA levels and compared with patients in the control arm. They will also report greater self-rated adherence to physiotherapists’ recommendations compared with the patients in the control arm. Compared with physiotherapists in the control arm, physiotherapists in the experimental arm will rate their patients as more adherent during physiotherapy sessions.

2. Patients in the experimental arm will report significantly decreased pain, increased function, greater low back pain (LBP)-related well-being and greater perceived global improvement after treatment compared with their pre-intervention scores, and compared to patients in the control arm.

3. Compared with their pre-treatment scores and compared with patients in the control arm, patients in the experimental arm will report significantly lower fear-avoidance beliefs and controlled motivation, as well as significantly greater competence and autonomous motivation.

4. Patients in the experimental arm will rate their physiotherapists as significantly more autonomy supportive than patients whose physiotherapists were assigned to the control arm. As a result of heightened self-awareness that comes from participation in communication skills training, physiotherapists assigned to the experimental arm will rate themselves as less autonomy supportive than physiotherapists assigned to the control arm. Independent raters of audio recordings of patient-physiotherapist interactions will rate experimental arm physiotherapists as more autonomy supportive than physiotherapists assigned to the control arm. Physiotherapists in the experimental arm will employ the specific communication strategies taught in the workshops with higher quality than physiotherapists from the control arm (who will not attend these workshops).

5. The influence of the experimental manipulation on outcomes (pain, function, and well being) will be mediated by patients’ rating of the physiotherapist’s autonomy support, perceived competence, autonomous motivation, fear-avoidance beliefs and adherence (see Figure 2).

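### The base sample size of 156 comes from a one-sided 5% test; at a two-sided .05 the plan has about 70% power with 254 patients and 74–76% with 292, not 80% or more

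*Protocol article*

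**What the plan says.** All of the relevant text is in the protocol article, Sample size. Pilot effects were d = .4 for adherence and satisfaction with back pain, and d = .5 for walking. The calculation takes d = .4 and gives the number for 80% "power (α = .05) to detect a between arm effect of d = .4 in a non-clustered RCT, using a t-test, would be 156", split as 78 per arm. For clustering, "we estimated that the ICC would be 0.03"; with 22 patients per clinic this gives a factor of 1.63. The section then states that "the study would require 254 participants to achieve 80% power for the adherence and LBP related data". A further 15% for loss to follow-up gives 292, and the section closes by saying that "our intended sample of 292 patients will provide more than 80% power to detect significant effects in these primary outcomes".

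Sidedness is not given there. Under Hypotheses, the expected effects are worded with a direction, for example "Patients in the experimental arm will report significantly greater weekly physical activity (PA) participation compared with their pre-treatment PA levels". Under Statistical methods, a treatment dummy in a linear mixed model is used to test differences in mean levels and rates of change, with week 24 as the primary endpoint. No one-sided test is mentioned in any section.

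**The concern.** The section gives every input to a standard calculation, so its result can be checked. For d = .4 with 80% power, a figure of 78 per arm is well below the familiar two-sided answer of about 100 per arm. The gap is 22%, too large to come from rounding or from a normal approximation in place of the t distribution.

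The base figure feeds both later sample sizes, so an error here undermines each power claim in the section. Adherence is the trial's stated aim and a primary outcome. A null adherence result at week 24 would be read as coming from a trial with more than 80% power to find d = .4, when the real chance of finding it at a two-sided .05 is nearer 70–76%.

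**Working it through.** **Inputs** (Sample size section unless noted): d = .4; α = .05, sidedness not stated; power 80%; two equal arms; t-test; ICC 0.03; m = 22; loss 15%; 12 centers (Centers section).

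**Step 1. Base sample size.** Normal approximation: n per arm = 2(z_α + z_β)² / d².

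- One-sided .05: 2(1.645 + 0.842)² / 0.16 = 77.3, so 78.
- Two-sided .05: 2(1.960 + 0.842)² / 0.16 = 98.1, so 99.

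Exact noncentral-t solution:

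- One-sided: 77.97, so 78 per arm and 156 in total. This is the protocol's figure.
- Two-sided: 99.08, so 100 per arm and 200 in total.

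At 78 per arm, power is 80.0% one-sided and 69.9% two-sided.

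**Step 2. The later steps reproduce.**

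- Design effect: 1 + (22 − 1) × 0.03 = 1.63.
- 156 × 1.63 = 254.3, so 254.
- 254 × 1.15 = 292.1, so 292.

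The discrepancy therefore lies in the first step alone.

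**Step 3. Two-sided power of the planned sizes at d = .4.** Effective n = N / [1 + (m − 1) × 0.03], then the noncentral-t power with half of that in each arm.

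| Patients analysed | m | Design effect | Effective n | Two-sided power | d detectable at 80% |
|---|---|---|---|---|---|
| 254 | 22 | 1.63 | 155.8 | 69.9% | .45 |
| 292 | 22 (held) | 1.63 | 179.1 | 75.9% | .42 |
| 292 | 292/12 = 24.3 | 1.70 | 171.8 | 74.1% | .43 |
| 248 (292 × 0.85) | 248.2/12 = 20.7 | 1.59 | 156.1 | 69.9% | .45 |

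No row reaches 80%. One-sided, 254 gives 80% and 292 gives 83–85%, which agrees with the protocol's claims.

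**Step 4. What a two-sided calculation would have given.** 200 × 1.63 = 326 before loss; with the protocol's own inflation, 326 × 1.15 = 375.

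**Step 5. Few clusters.** The figures above ignore that there are only 12 centers. Testing on 10 between-center degrees of freedom lowers two-sided power to about 62% at 254 and 66–68% at 292. This is a separate matter, and the finding does not depend on it.

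**The case against.** The strongest reply is that sidedness is unstated rather than wrong. Most hypotheses carry a direction, and a one-sided 5% test reproduces 156, 254 and the claim for 292. That is fair as an account of how the number may have arisen. But directional wording does not declare a one-sided test, the analysis section speaks of differences, and the fourth hypothesis predicts lower self-ratings by trained physiotherapists alongside higher ratings by patients and independent raters. Readers will take a bare .05 as two-sided. If one-sided testing was intended, the text still needs correcting, because it has to say so.

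A second reply is that the mixed model recovers the power. The section credits it only with making loss to follow-up harmless. Granting that in full means using all 292 patients, which gives 74–76%. Baseline adjustment could help pain, disability, quality of life and self-reported activity: with a baseline correlation of .3 to .5 (an assumption; the protocol gives none), two-sided power at 292 over 12 centers would be about 78–85%. It cannot help the adherence scales, which have no pre-treatment measurement in Table 3, and the stated calculation is a plain t-test.

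Third, at the d = .5 quoted for walking, two-sided power is about 87% with 254 and 90–91% with 292. That stands, but the 80% is claimed for the adherence and back pain data, which were sized on d = .4.

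Finally, an analysis plan that is not shown might fix the sidedness. It could not make 156 the two-sided answer.

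**Conclusion.** The concern holds. The figure of 156 is the one-sided 5% answer, and nothing in the protocol declares a one-sided test. At a two-sided .05 and d = .4, 254 patients give about 70% power. The full 292 give 74% with the cluster size implied by 12 centers, or 76% with the factor held at 1.63. The risk of missing d = .4 is therefore about 24–30%, and the effect detectable with 80% power is about .42 to .45.

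These figures use the protocol's ICC, its t-test basis and equal clusters. They take no credit for repeated measures or baseline adjustment, which the protocol does not quantify, and make no deduction for the small number of centers. The conclusion concerns the outcomes sized on d = .4, not walking at d = .5.

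**What to change.** In the Sample size section:

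- State that all tests are two-sided at .05.
- Replace 156 (78 per arm) with 200 (100 per arm), and show that the same clustering factor then gives 326 before loss.
- If feasibility fixes recruitment at 292, say so, and present 292 as the achievable number rather than as the result of the calculation.
- Replace the claims of 80% and more than 80% with the two-sided figures: about 70% at 254 and 74–76% at 292 for d = .4, or equivalently 80% power for d of about .42 to .45.

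If the sponsor did intend one-sided 5% tests, the alternative is to declare this in the sample size and statistical methods sections, justify it, and hold the analysis to it.

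The cost is a rewritten paragraph. No extra patients and no change of design are needed, but the stated power becomes less favourable.

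### The base sample size of 156 is a one-sided figure, but no one-sided test is declared; under two-sided testing, power for adherence is about 70–76% at d = .4, not above 80%

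*Protocol article*

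**What the plan says.** The Sample size section of the protocol article builds the trial size in three steps.

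- **Base size.** It gives "the estimated sample required for 80% power (α = .05") and reports that the number needed "to detect a between arm effect of d = .4 in a non-clustered RCT, using a t-test, would be 156", that is 78 per arm.
- **Clustering.** It takes an ICC of 0.03 and 22 "patients per clinic, the correction factor is 1.63 for our cluster-randomized design", which brings the total to 254.
- **Loss to follow-up.** It expects about 15% loss and says that one would traditionally "increase the sample size by 15% to 292 participants (146 per arm"). It then argues that mixed models make the loss negligible.

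It concludes that "our intended sample of 292 patients will provide more than 80% power to detect significant effects in these primary outcomes".

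The section does not say whether α is one- or two-sided. Statistical methods plans linear mixed models with a dummy-coded treatment variable, takes week 24 as the primary endpoint, and is also silent on sidedness. Most of the Hypotheses are worded in one direction, for example "Patients in the experimental arm will report significantly greater weekly physical activity (PA) participation compared with their pre-treatment PA levels". None of them sets a one-sided significance level.

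**The concern.** An unqualified α of .05 is ordinarily read as two-sided. On that reading 156 is too small for the stated inputs by about 44 patients before clustering (200 − 156), and the later steps multiply the shortfall.

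The Sample size section is the only justification given for the size of the trial. If it overstates power, a null result on adherence, the outcome named in the trial's aim, would be read as coming from an adequately powered trial. The chance of missing a true d of .4 would be about 24–31% rather than below 20%.

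**Working it through.** **Inputs (all from Sample size, except the number of centers, from the Centers section):** d = .4; power 80%; α = .05; ICC .03; m = 22; loss 15%; N = 292; 12 centers.

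**1. Reproduce 156.** By the normal approximation, n per arm = 2(z_α + z_β)²/d².
- One-sided: 2(1.645 + 0.842)²/0.16 = 77.3, so 78 per arm, 156 in total.
- Two-sided: 2(1.960 + 0.842)²/0.16 = 98.1, so 99 per arm, 198 in total.

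The exact noncentral-t calculation agrees:

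| n per arm | One-sided power | Two-sided power |
|---|---|---|
| 77 | 79.6% | 69.4% |
| 78 | 80.0% | 69.9% |
| 99 | 87.7% | 79.97% |
| 100 | 88.0% | 80.4% |

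So 78 is the exact one-sided minimum, and the two-sided minimum is 100 per arm.

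**2. Reproduce the later steps.** Design effect 1 + 21 × .03 = 1.63; 156 × 1.63 = 254.3; 254 × 1.15 = 292.1. Both follow correctly from 156, so they inherit its sidedness. The same chain from 200 would give 200 × 1.63 = 326 before loss.

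**3. Power of the planned 292 at d = .4.** SE = √(4 × DE / N), with the outcome SD set to 1. Power by the normal approximation = Φ(.4/SE − z_α). Detectable d at 80% power, two-sided = (1.960 + 0.842) × SE. The mean cluster size is either the article's 22 or N/12.

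| Analysed N | m | DE | SE | Two-sided power | One-sided power | Detectable d (two-sided) |
|---|---|---|---|---|---|---|
| 292 | 22 | 1.63 | .1494 | 76.3% | 84.9% | .42 |
| 292 | 24.3 | 1.70 | .1526 | 74.6% | 83.6% | .43 |
| 248 (15% lost) | 22 | 1.63 | .1621 | 69.4% | 79.5% | .45 |
| 248 (15% lost) | 20.7 | 1.59 | .1601 | 70.5% | 80.3% | .45 |

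Using a t reference with patient-level degrees of freedom lowers the two-sided figures by about half a point (75.9%, 74.1%, 68.9%, 70.0%).

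**4. Sensitivity to the small number of centers.** With 12 centers in two arms, a center-level comparison has about 12 − 2 = 10 degrees of freedom. With the same SEs and a noncentral t on 10 df:

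| Analysed N | DE | Two-sided power | One-sided power | Detectable d (two-sided) |
|---|---|---|---|---|
| 292 | 1.63 | 67.5% | 80.1% | .46 |
| 292 | 1.70 | 65.7% | 78.6% | .47 |
| 248 | 1.63 | 60.6% | 74.3% | .50 |
| 248 | 1.59 | 61.6% | 75.2% | .50 |

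**5. Baseline availability.** Table 3 shows no pre-treatment assessment for any adherence measure. Pain, bothersomeness, disability, patient-specific function, quality of life and self-reported physical activity all have one.

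**The case against.** **The hypotheses are directional, so a one-sided test may have been meant.** This stands in part. On a one-sided .05 test the claim holds with no loss by the normal approximation (about 84–85%). But directional wording does not set a significance level, and the article would have to declare the test. With 10 df the one-sided figure is only about 79–80% with no loss.

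**The mixed model may gain precision.** For the back pain outcomes it may. If the baseline correlation were .4 to .5 (an assumption; the article gives none), two-sided normal power with 292 and design effect 1.70 would be about 82–86%, and at .3 about 78%. The article's own calculation is a t-test and quantifies no such gain, and adherence has no baseline to supply it. For this reason the conclusion is confined to adherence.

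**Stronger readings that the article does not support:**

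- *That m = 22 understates the clustering.* It lies between 254/12 = 21.2 and 292/12 = 24.3. After 15% loss the mean is 248/12 = 20.7, so 22 is then slightly cautious.
- *That without a baseline the mixed model cannot recover anything from dropouts.* Patient-rated adherence is collected at weeks 1, 4, 12 and 24, so earlier visits can contribute. The 69–70% figure treats lost patients as contributing nothing and is a lower bound in that respect.
- *That true power is simply 61–68%.* Most of that drop comes from the 10-df reference, which is separate from the sidedness error. The article fixes no degrees-of-freedom method, and a protocol article commonly leaves it to the analysis plan.
- *That adding 15% instead of dividing by 0.85 is a material error.* 254/0.85 = 299 against 292 is a difference of about 2%.

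**Conclusion.** The point holds. The 156 reproduces from the stated inputs only as a one-sided .05 calculation, and the article declares no such test. The two-sided figure is about 200.

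For adherence at d = .4, ICC .03 and two-sided .05, unadjusted power with 292 patients is about 75–76% with no loss and about 69–70% if 15% contribute nothing at week 24. Even the most favourable of these, which uses the article's own design effect and assumes complete follow-up, is below 80%. A few-cluster reference of about 10 df widens the range down to about 61%, as a sensitivity result.

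The shortfall is conditional on two-sided testing. A reader might infer that the trial is underpowered for every primary outcome or must recruit more patients. Neither follows: outcomes with a baseline may do better, and for physical activity (walking) the article cites a larger pilot effect, d = .5. What is wrong is the power statement, which is cheap to correct.

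**What to change.** In the Sample size section:

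1. State whether the test is one- or two-sided.
2. If two-sided, say that 156 is a one-sided figure. For adherence, replace the claim of power above 80% with about 70–76% at d = .4, or a detectable d of about .42 to .45.
3. Present the negligible effect of loss to follow-up as an unquantified assumption.
4. Add the sensitivity range for 12 centers with about 10 df: two-sided power about 61–68%, detectable d about .46 to .50.
5. If a one-sided .05 test was intended, declare it explicitly. Report power of about 84–85% with no loss by the normal approximation, and about 79–80% with 10 df.

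The cost is wording only, with a less favourable power statement if the test is two-sided. No additional patients and no design change are needed.
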